### 2.9 Statistical analysis

All data will be analyzed using the Independent Samples *t*-test model in SPSS Version 26 to compare age, time of new ulcer eruption, pain scores (VAS), and ulcer size. The Chi-Square test will be employed to compare gender distribution, distribution of RAS on mucosal epithelium, history of drug allergies, and dietary habits. The significance level for statistical tests was set at α = 0.05, with a confidence level of 80% (Ghorbani et al., 2020; Shao and Zhou, 2020).

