## Abstract

**Background:** Recurrent Aphthous Stomatitis (RAS) is a common ulcerative disease of the oral mucosa which is characterized by pain, and recurrent lesions in the oral cavity. This condition is quite painful, causing difficulty in eating, speaking and swallowing. Topical medications have been used for this condition, but the obstacle in using topical medications is the difficulty of achieving drug effects due to saliva wash out. This problem can be overcome by film hydrogel formulation which can protect the ulcer and reduce the pain to some extent. α-mangostin is a xanthone isolated from the rind of the mangosteen fruit. One of the activities of α-mangostin is anti-inflammatory effects, which operate through the characteristic mechanism of inhibiting the inflammatory response. This protocol study aims to investigate the efficacy of an α-mangostin hydrogel film with a chitosan alginate base for recurrent aphthous stomatitis (RAS) in comparison with a placebo over a period of 7 days.

**Study design:** This is a two-arm, double blinding, randomized controlled trial enrolling patients with RAS. The efficacy test of α-mangostin Hydrogel Film will be tested against the placebo. Patients with RAS will be allocated randomly into the two arms and the hydrogel film will be administered for 7 days. The diameter of ulcer and visual analog scale (VAS) score will be used as the primary efficacy endpoint. The outcome measure will be compared between the two arms at the baseline, day 3, day 5, and at the end of 7 days.

**Discussion:** The purpose of this clinical research is to provide scientific evidence on the efficacy of α-mangostin hydrogel film with a chitosan alginate basis in treating recurrent aphthous stomatitis. The trial is expected to improve our capacity to scientifically confirm the anti-inflammatory effectiveness of α-mangostin compounds in a final formulation that is ready to use.

**Trial registration:** NCT06039774 (14 September 2023).

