## 2 Methods

### 2.1 Study design

This is a two-arm, double-blinded, randomized controlled trial scheduled to take place at the Padjadjaran University Dental and Oral Hospital in Bandung, Indonesia. The trial aims to evaluate the efficacy and safety of α-mangostin hydrogel film in comparison to a placebo. Patients diagnosed with RAS will be randomly assigned to one of the two arms, and they will receive the mucoadhesive film for a duration of 7 days. The primary efficacy endpoints will be determined based on the measurement of ulcer diameter and the use of the Visual Analog Scale (VAS) score. These outcome measures will be assessed at various time points, including prior to the initial visit (baseline), on day 3, day 5, and at the conclusion of the 7-day treatment period based on previous trial on 2020 and 2022 (Ghorbani et al., 2020; Molania et al., 2022).

Ethics approval has been obtained from Research Ethics Committee of the Faculty of Medicine, Universitas Padjadjaran, Indonesia (approval reference number: 806/UN6.KEP/EC/2023). The trial was registered in the Clinicaltrials.gov registry (Trial number NCT06039774).

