### 2.5 Sample size

Sample size was calculated with the lemeshow formula. Calculations were performed using 80% power, a 5% significance level, and 20% dropout rate. The required sample size was approximately 19 subjects for each group. We plan to enroll 24 subjects in each group to allow for a 20% withdrawal rate.

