**FIGURE 1 F1:**
[figure not shown]
Flowchart of study protocol.

Patients in group 1 will receive α-mangostin hydrogel films with a chitosan-alginate base in the form of a patch. Each patch consists of 0.25 mg α-mangostin, 2% of alginate sodium, 0.2% of chitosan, 1% of glycerin, pure ethanol, and aquades. The patch is applied to the affected oral area twice daily (after breakfast and dinner) for a duration of 1 h. The patients will be advised to refrain from eating and drinking during patch application for up to 1 h post-application. In the event of a missed application of the test substance, participants are encouraged to apply the patch as soon as possible. However, if it is approaching the time for the second evening application, participant should skip the initial dose, and proceed to apply the second patch after dinner as scheduled. Participants are required to notify the researcher during evaluation and monitoring if such deviations occur. The supervision of therapy application by a pharmacist acting as the principal investigator is integral to this process.

Patients in group 2 will receive the placebo film with the same materials but without active ingredient or α-mangostin and apply with the same instructions that were provided to group 1.

The use of mouthwash, antihistamines, immunosuppressive agents, antibiotics, and analgesics is strictly prohibited during the clinical efficacy trial period. Visual analog scale records and sheets for noting side effects/adverse drug reactions are provided throughout the testing phase. Participants are instructed to record pain scores daily during the ulcerative stage and to document any side effects associated with the film usage. Ulcer size is documented on days 1 (baseline), third, fifth, and seventh. Record sheets and any remaining hydrogel film are collected at the end of the study. Participants are directed to promptly discontinue film usage if rash or oral mucositis appears during the trial and report any occurrences to the supervising physician and researcher.

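### Both primary endpoints are tested by independent-samples t-test with no baseline covariate, although each is measured at baseline; ANCOVA would usually be more precise and would correct chance imbalance

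*Protocol article*

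**What the plan says.** The Abstract names the primary endpoints: "The diameter of ulcer and visual analog scale (VAS) score will be used as the primary efficacy endpoint". Section 2.1 gives both a baseline measurement: "These outcome measures will be assessed at various time points, including prior to the initial visit (baseline), on day 3, day 5". Section 2.8 repeats this for ulcer size: "Ulcer size is documented on days 1 (baseline), third, fifth, and seventh".

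The analysis is fixed in Section 2.9, which opens "All data will be analyzed using the Independent Samples" t-test and applies it "to compare age, time of new ulcer eruption, pain scores (VAS), and ulcer size". The two primary endpoints thus share a method, and a sentence, with age and time of ulcer eruption. The section names no covariate, change score or repeated-measures model. The one stated role for the baseline values is in the Abstract: "The outcome measure will be compared between the two arms at the baseline, day 3, day 5, and at the end of 7 days".

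Section 2.5 asks for about 19 subjects per group at 80% power and 5% significance, and adds: "We plan to enroll 24 subjects in each group to allow for a 20% withdrawal rate". Section 2.6 describes a computer-generated random sequence and mentions no stratification by ulcer size or pain.

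**The concern.** How large and painful an ulcer is a few days into treatment is likely to depend in part on how large and painful it was at the start. With about 20 people per arm and no stratification described, the arms can differ noticeably at baseline by chance. A plain t-test carries part of any such difference into the estimated treatment effect, and testing the baseline difference for significance does not remove it. The t-test also leaves in its error term the outcome variation that the baseline value could explain.

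What is at stake is power, and how far the result can be trusted if an imbalance is seen. The average validity of the test is not in question. The method is stated in the document, so this is not a detail left to an unseen analysis plan.

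**Working it through.** **Inputs.** From the protocol article: 19 evaluable and 24 enrolled per group, 80% power, 5% significance, 20% withdrawal (Section 2.5); independent-samples t-test (Section 2.9). Assumed: two-sided testing (sidedness is not stated), equal variances across arms and visits, and a baseline-outcome correlation r from 0.1 to 0.7. The documents give no value for r.

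**1. The plan's own figure.** 19/(1 − 0.20) = 23.75, rounded up to 24. This reproduces. The 19 cannot be rebuilt, because no effect size or SD is given.

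**2. Implied effect.** Solving the two-sided 5% t-test (36 df) for 80% power at 19 per arm gives a standardised difference d = 0.934. The normal approximation gives (1.960 + 0.842) × sqrt(2/19) = 0.909. The value 0.934 is used below. It is a back-solved figure, not one the protocol states.

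**3. Chance imbalance.** The SD of the difference in baseline means is sqrt(2/n) baseline SDs.

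| n per arm | SD of baseline difference | chance above 0.3 SD | chance above 0.5 SD |
|---|---|---|---|
| 24 | sqrt(2/24) = 0.289 | 30% | 8% |
| 19 | sqrt(2/19) = 0.324 | 36% | 12% |

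An imbalance b shifts the unadjusted estimate by r × b. With r = 0.5 and b = 0.5 the shift is 0.25 SD, against an implied effect of about 0.93 SD. The type I error conditional on that imbalance is about 10% at 24 per arm and 9% at 19. With r = 0.5 and b = 0.3 it is about 5% and 4%, so only the larger and rarer imbalances matter here.

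**4. Power of ANCOVA at 19 per arm, with its cost.** The variance relative to the unadjusted t-test is (1 − r²) × [1 + 1/(2n − 4)]. The bracket is the average cost of estimating the slope; at n = 19 it is 1 + 1/34 = 1.029. The error df fall from 36 to 35. The noncentrality is 0.934 × sqrt(19/2) = 2.88, divided by the square root of the relative variance.

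| r (assumed) | relative variance | power |
|---|---|---|
| unadjusted t-test | 1 | 80% |
| 0.1 | 0.99 × 1.029 = 1.02 | 79% |
| 0.2 | 0.96 × 1.029 = 0.99 | 80% |
| 0.3 | 0.91 × 1.029 = 0.94 | 82% |
| 0.5 | 0.75 × 1.029 = 0.77 | 89% |
| 0.7 | 0.51 × 1.029 = 0.52 | 97% |

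Break-even is where (1 − r²) × 1.029 = 1, that is r = sqrt(1 − 1/1.029), or about 0.17.

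**5. If change from baseline is tested instead.** With equal variances its variance factor is 2(1 − r). The excess over ANCOVA's 1 − r² is 2(1 − r) − (1 − r²) = (1 − r)², which is never negative. Apart from the small slope cost, a change-score t-test is therefore never more efficient than ANCOVA. Its factor exceeds 1, making it worse than comparing follow-up values, when r is below 0.5.

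**The case against.** The strongest defence is that nothing is invalid. Randomisation keeps the unadjusted t-test unbiased on average with 5% type I error, and its standard error already allows for chance imbalance. That stands. A reader might infer that the planned analysis is biased, but the documents do not support this: the harm is conditional on an imbalance that has actually occurred, and otherwise the loss is one of efficiency.

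A second objection is that the gain rests on an unstated effect size and an unstated correlation. This also stands, and it is why the range above runs down to 0.1. Low correlation is plausible. Section 2.4 admits only minor ulcers diagnosed within 48 h of appearance, which may narrow the spread of baseline size. Section 3 puts duration at 4 to 14 days, so some ulcers may have healed by day 7.

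Two further inferences go beyond the text:

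- **That follow-up values are tested and baseline is ignored.** The Abstract's comparison at each visit makes this the likelier reading, but Section 2.9 does not exclude change scores. Step 5 shows that the recommendation survives either way.
- **That visit-by-visit t-tests will discard anyone absent that day.** The document does not say how missing days are handled, an article commonly leaves this to the full protocol or analysis plan, and the 20% in Section 2.5 is only a sample-size allowance. No criticism on missing data is made here.

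Nor do the documents make a full repeated-measures model necessary. For about 19 evaluable per arm, single-day ANCOVA captures the essential gain.

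**Conclusion.** The point holds as a recommendation to improve a stated method. Section 2.9 compares both primary endpoints without a baseline covariate, although each has a baseline value. The test is valid on average, but it gives up precision and leaves a chance imbalance uncorrected.

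If the implied effect of about 0.93 SD is right, adjustment takes power at 19 per arm from 80% to 82% at correlation 0.3, 89% at 0.5 and 97% at 0.7. There is no material change at 0.2, and about one percentage point is lost at 0.1. The SDs of the chance imbalance depend only on the group sizes. The power figures depend on the back-solved effect, two-sided testing and the assumed correlations.

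**What to change.** By a dated amendment before unblinding, replace the t-test for each primary endpoint with an ANCOVA of the day 7 value, or of the value at another single day named as primary in advance. The terms are arm and the baseline value of the same endpoint, taken before the first film is applied. Present baseline characteristics descriptively, without significance tests between arms.

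A mixed model over days 3, 5 and 7 with baseline as covariate is an acceptable alternative, provided the contrast at the named day is declared primary.

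This needs no extra participants, visits or measurements, and SPSS, the package already named, fits both models. The statistical cost is one degree of freedom and a negligible loss of power if the correlation is very low. The administrative cost is the amendment itself: the t-test is in the published protocol and Section 4 reports that recruitment began in December 2023, so the change must be documented as made without sight of results by arm.

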### 2.10 Data and safety monitoring

To safeguard patient privacy, all research data will be handled in line with Hospital Authority and Hospital’s policy in handling, storage, and destruction of participant’s medical record. The data will be securely stored in cabinets exclusively designated for protecting participants’ confidential information within the department. Additionally, all gathered data will be input into a computer with restricted access to investigators. The retained participant information will be stored for a period of 5 years post-study and subsequently will then undergo a secure destruction process.

## 3 Discussion

Recurrent Aphthous Stomatitis (RAS), also known as recurrent aphthous ulceration (RAU) or commonly referred to as canker sores, is a prevalent condition characterized by recurring circular ulcers that affect the oral mucosal layers. RAS entails inflammation occurring within the oral mucosal layer. This condition often arises due to hormonal changes, physical stress, trauma, alterations in psychological conditions, chemical irritations, and is even associated with allergies and genetic factors. Irritation can manifest in any part of the oral cavity, with a duration ranging from 4 to 14 days (Tarakji et al., 2015). It is recognized as one of the most painful inflammatory ulcerative conditions in the oral cavity, causing discomfort during eating, swallowing, and speaking (Moghadamnia, Motallebnejad and Khanian, 2009).

A range of medications, sourced from natural or synthetic origins, is utilized as treatments for RAS. These therapies exhibit diverse mechanisms of action, encompassing anti-inflammatory, antioxidant, immunomodulatory, analgesic, wound healing, antiulcer, antibacterial, antiviral, and antibiotic effects (Dhama et al., 2018). Alternative therapy for patients with RAS may involve the use of herbal remedies, such as α-mangostin derived from the rind of the mangosteen fruit (*Garcinia mangostana* L.). Several studies indicate that mangosteen peel extract containing α-mangostin exhibits potent antioxidant activity and the ability to promote wound healing. This suggests its potential effectiveness in formulating pharmacologically beneficial agents for wound healing (Fajeriyati, Muchtaridi and Sopyan, 2021).

A rat excision wound model was employed to investigate the effects of α-mangostin on wound healing. According to their findings, topical application of α-mangostin ointment enhanced the wound healing process. Parameters utilized in the experiment included wound closure duration and wound contraction. On the 20th day post-treatment with α-mangostin, a 90% wound healing rate was observed in the treated group. Based on their research, these results affirm that α-mangostin possesses wound healing properties (Sasikala Chinnappan et al., 2020).

Based on research, α-mangostin has gained recognition as an agent for oral cavity therapy associated with inflammatory events (Wathoni et al., 2019). In silico modeling indicates that α-mangostin exhibits the lowest binding energy with cyclooxygenase-2 (COX-2) and nuclear factor kappa-light-chain-enhancer of activated B (NFκB) proteins. α-mangostin has been found to inhibit the production of prostaglandin-E2 (PGE2), nitric oxide, and the expression of inducible nitric oxide synthase (iNOS) protein. Tumor necrosis factor-α (TNF-α) and interleukin-6 (IL-6) cytokines were significantly inhibited at concentrations of 8 and 14 g/mL. At higher doses, α-mangostin inhibits NFκB translocation while suppressing COX-2 enzyme, but not COX-1. α-mangostin inhibits total leukocyte migration, particularly *in vivo* neutrophils. Levels of TNF-α and IL-1β significantly decreased in peritoneal fluid, as measured by enzyme-linked immunosorbent assay (ELISA) analysis. Overall, these findings indicate that α-mangostin acts effectively as an anti-inflammatory agent through various mechanisms involving the inhibition of inflammation (Mohan et al., 2018).

Several previous studies also showed the use of herbal remedies to treat RAS. These treatments have shown efficacy in diminishing pain, reducing the number of ulcers, minimizing ulcer size, and expediting the healing duration. Limonene in citrus essential oil demonstrates antiulcerogenic activity. This antiulcerogenic effect of limonene functions as an immunomodulatory agent for oral aphthous ulcers. The mechanism underlying these properties is linked to its ability to boost mucus secretion, heat shock protein-70, vasoactive intestinal peptide, and prostaglandin E2 (Moraes et al., 2009). Enhancing wound healing through supportive treatments is also crucial in RAS, studies conducted in *in vitro* setting have revealed that the compound 7-O-(β-D-glucopyranosyl) galactin, present in *Ageratina pichinchensis*, has the ability to stimulate the proliferation of normal human skin cells (HFS-30) that contributes to the acceleration of wound healing (Romero-Cerecero, Zamilpa and Tortoriello, 2015). Sage extract, recognized as a natural antioxidant, has been utilized in RAS treatment. The phenolic and flavonoid compounds within sage extract have the ability to boost blood oxygen levels and safeguard the body from oxidative stress and free radicals, mitigating the risk of cell damage and providing protection against various types of ulcers (Mohammed and Abdulraheem, 2021).

The primary approach to addressing RAS involves the use of topical medications, which are deemed more cost-effective, efficient, and safe. Challenges encountered in the use of topical medications include difficulties in achieving the desired therapeutic effects. This is attributed to the common obstacle of drug delivery to the oral mucosa, known as “saliva washout,” resulting in the removal and rinsing of the drug on the mucosal surface. This issue can be addressed through the formulation of mucoadhesive film preparations, which can protect ulcers, create a barrier against external stimuli, and reduce pain to a certain extent (Suharyani et al., 2021).

Hydrogels exhibit highly favorable characteristics, including maintaining a moist environment at the wound base, absorbing minimal wound exudate, and soothing the wound surface (Zhang et al., 2018). Its insoluble hydrophilic structure demonstrates exceptional potential for absorbing wound exudate and allowing oxygen diffusion to expedite the healing process (Dhama et al., 2018). Hydrogels exhibit a distinctive capability to function as a tissue prototype, aiding in the restoration of essential components within undamaged tissue at the injury site until the process regeneration and regulation of the wound area are finalized (Dimatteo, Darling and Segura, 2018). Hydrogel films represent a three-dimensional dosage form with a hydrogel base, utilizing one or a combination of polymers to absorb and deliver active substances at the therapeutic site (Yuniarsih, Muchtaridi and Wathoni, 2018; Tran and Tran, 2019).

The hydrogel film dosage form in transdermal delivery offers several advantages, as elucidated by Yang and Pierstorff (2012) (Yang and Pierstorff, 2012):1. Extended and Targeted Active Substance Release: Hydrogel films enable prolonged and targeted release of systemic active substances, providing better control over drug administration.2. Enhanced Bioavailability: Hydrogel films can enhance the bioavailability of active substances by protecting them from degradation and inactivation processes in the body, thereby improving treatment effectiveness.3. Improvement in Solubility of Poorly Soluble Drugs: Hydrogel films help improve the solubility of poorly soluble drugs in solvents, facilitating better absorption and distribution in the body.4. Higher Treatment Cost Efficiency: By increasing drug efficacy and reducing the required dosage to achieve a specific therapeutic effect, hydrogel films can enhance the cost efficiency of treatment.5. Reduction in Administration Frequency and Risk of Dosing Errors: Hydrogel films allow for a reduction in the frequency of drug administration, which can improve patient compliance while lowering the risk of dosing errors due to more controlled formulations.

A study demonstrated that an *in vivo* investigation of α-mangostin hydrogel films with a chitosan-alginate base for RAS therapy exhibited a favorable healing response, achieving a healing rate of 93% on the seventh day (Milanda et al., 2022). These promising outcomes have motivated us to conduct a Clinical Trial of α-mangostin Hydrogel Films with a Chitosan-Alginate Base with the aim of evaluating the clinical efficacy and safety in treating patients with RAS.

## 4 Trial status

The recruitment of participants started in December 2023 and is ongoing.

## Data Availability

The original contributions presented in the study are included in the article/Supplementary Material, further inquiries can be directed to the corresponding author.
